# STUDY TREATMENTS

- 1. **Treatment Arms**

**5.1.1 Description**

The hypothesis will be tested in children with tetralogy of Fallot undergoing elective open heart surgery with standard heart arrest and cardiopulmonary bypass. An informed consent will be obtained from all the patients’ parents or guardians. 40 patients will be recruited in to the study within two years. They will be randomized into 2 equal sized groups: Group I control (Sham, n=20) and Group II preconditioning (RIPC, n=20).

**5.1.2 Dosage and Route of Administration: RIPC Protocol**

RIPC will be instituted by four 5-minute cycles of leg ischemia with intervening 5 minutes of reperfusion immediately following induction of standard anaesthesia in the operating room. A standard WelchAllen blood pressure cuff is placed on the mid-to upper thigh of the leg which is free of i.v./arterial lines. Inflating the blood pressure cuff to a pressure exceeding the patient’s systolic pressure by 30 mmHg will constrict the site to interrupt local blood flow and thus perfusion of the lower leg (i.e. if systolic pressure is 70mmHg then the cuff will be inflated to 100mmHg). The cuff would be deflated to permit reperfusion. Blood flow interruption and restoration will be monitored by standard pulse-oxymetry. Control patients will have sham placement of cuff without inflation. RIPC will be performed after the patient has been anesthetised while routine central lines are being placed. The protocol is safe and has been previously applied in children by us without any complications or adverse consequences as we have previously published and as is the case with our study in progress at the RCH (HREC#26091C).

**5.1.3 Heart surgery**

Anaesthetics and bypass protocol will not change from the usual practice within the hospital. Open heart surgery for tetralogy of Fallot will be performed in a standard fashion with cardioplegic heart arrest and cardiopulmonary bypass. Our group has demonstrated expertise in studying patients undergoing heart surgery (17, 22, 25-29).

**5.1.4 Myocardial sampling**

Muscular obstruction of the right ventricular outflow tract will be resected in routine fashion following administration of standard cardioplegic solution. Resected right ventricular myocardium that is routinely discarded (approximately 10-15mg – pea size) will be saved and processed for mitochondrial function and histological measures. As per our previously published studies in children undergoing resection of the right ventricular outflow obstruction, myocardial samples are immediately transferred on ice for laboratory assays (24, 27).

**5.1.5 Blood sampling**

The following 5 blood samples (6.5 ml each) will be taken from the arterial line that is routinely placed in all patients: baseline, immediately after discontinuation of CPB, at 6, 12, and 24 hours following discontinuation of CPB. No additional lines or invasive procedures will be performed apart from those that routinely required for heart surgery. From each sample, 1.5 ml will be used for proteomic assays, and 5 ml for the lymphocyte mitochondrial function assays.

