# PROTOCOL SYNOPSIS

| Title | The protective effect of remote ischaemic preconditioning in congenital heart disease patients undergoing cardiopulmonary bypass surgery |
| --- | --- |
| Objectives | Support of the circulation during heart surgery using the heart-lung bypass machine is inevitably associated with organ damage and associated reduced function. This is due to reduced blood flow (ischaemia), the effects of restoration of flow (reperfusion injury) and the subsequent inflammation that is caused. The body has its own way of protecting itself against reduced blood flow and oxygen by a mechanism known as preconditioning. In essence, brief periods of mild ischaemia are protective against a subsequent more severe episode of ischaemia. These periods of mild ischaemia can be of the organ itself or of another organ in the body. For example ischaemia of the leg can protect the heart against ischaemia, so called “remote preconditioning”. We have shown in animal and human models that remote preconditioning using a tourniquet placed around a thigh for brief periods (similar in duration to when taking blood samples from children) reduces the amount of injury to heart muscle by 50% and also leads to improved heart and lung function. We have shown that remote preconditioning in a similar way protects the organs of a heterogeneous group of children undergoing cardiac surgery, resulting in better function of the heart and lungs and also a reduction of the inflammatory response to the heart-lung machine. This could potentially reduce the problems in looking after children after surgery and also reduce the amount of time spent in the intensive care unit.  We will study a more uniform group of patients undergoing cardiac surgery in the neonatal period inorder to identify key protein and metabolic changes that occur within this cardioprotective protocol. All interventions will be performed during the period of routine general anaesthesia at the time of surgical repair. We will study the degree of organ injury induced by heart-lung bypass using standard intensive care parameters and equipment for measuring lung function. The degree of heart muscle and blood cell metabolic function will be assessed by laboratory tests. Samples will be taken from routinely discarded resected cardiac tissue and indwelling catheters routinely placed at the time of surgery and not require additional venepuncture. Measurements will be made prior to surgery and also at set time intervals in the first 24 hours postoperatively to determine the evolution of effects. |

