
- 1. **Research Question**

Based on the above background and our previous studies, we will endeavour to identify a plasma-borne factor produced by brief repetitive episodes of ischemia-reperfusion (IPC) in the thigh that induces a protective state in remote organs (remote ischemic preconditioning, RIPC). We will assess the global proteomic and mitochondrial metabolic response to IR injury in children undergoing heart surgery with CPB and the modification of such a proteomic response induced by remote IPC stimulus. Proteomic assessment and mitochondrial metabolism methodology will be employed concurrently.

- 1. **Rationale for Current Study**

We hypothesise that brief repetitive episodes of ischemia and reperfusion in the thigh release a plasma-borne factor that induces a protective state in remote organs and significantly modifies systemic inflammatory response to IR injury and modulates mitochondrial metabolic function in heart muscle and lymphocytes. These effects may afford augmented organ protection to neonatal children undergoing cardiopulmonary bypass surgery. Characterization and identification of the remote IPC protective factor and pathways that foster recruitment of innate protective mechanisms against organ dysfunction following IR injury will be crucial to tailoring more efficient and clinically practical protective therapy. The future clinical application of such protection could be immense and may ultimately encompass organ transplantation, protection against stroke, myocardial infarction, acute multi-organ dysfunction, and attenuation of systemic inflammatory response in diverse clinical scenarios.

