# STUDY DESIGN

- 1. **Type of Study**

Small randomised, blinded, surgical trial of preoperative therapy with highly regulated, brief, non-invasively-induced, localised leg ischaemia and reperfusion, for its capacity to invoke remote ischemic preconditioning-related molecular signalling in blood and heart muscle.

- 1. **Number of Subjects**

N=40 Total.

- 1. **Expected Duration of Study**

March 2010-March2012

- 1. **Primary and Secondary Outcome Measures**

**Primary outcome measures:** The identification of molecular signalling in blood and heart muscle in response to RIPC induced by highly regulated, non-invasively-induced, localised leg ischaemia (5min) and reperfusion (5min) for 4 cycles.

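### No blood sample is specified between the last cuff deflation and bypass, and baseline is not fixed before the first inflation, so direct release of a plasma factor cannot be told apart from a RIPC-altered response to bypass

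*Protocol*

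**What the plan says.** **Sampling.** Protocol section 5.1.5 states that "The following 5 blood samples (6.5 ml each) will be taken from the arterial line that is routinely placed in all patients", at these times: "baseline, immediately after discontinuation of CPB, at 6, 12, and 24 hours following discontinuation of CPB". Of each sample, "1.5 ml will be used for proteomic assays, and 5 ml for the lymphocyte mitochondrial function assays". Baseline is not defined further. The synopsis adds only that "Measurements will be made prior to surgery and also at set time intervals in the first 24 hours postoperatively", which places the first measurement before surgery but not before the cuff.

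**Intervention.** Section 5.1.2 applies "four 5-minute cycles of leg ischemia with intervening 5 minutes of reperfusion immediately following induction of standard anaesthesia" and adds that "RIPC will be performed after the patient has been anesthetised while routine central lines are being placed". It gives no order for arterial access, the baseline draw and the first inflation.

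**Aims.** Section 2.2 sets out to "identify a plasma-borne factor produced by brief repetitive episodes of ischemia-reperfusion (IPC) in the thigh", and also to assess how RIPC modifies the proteomic response to surgery. The primary objective (3.1) asks whether RIPC modifies the plasma proteomic and mitochondrial response of patients having congenital heart surgery. The primary outcome (4.4) is "The identification of molecular signalling in blood and heart muscle in response to RIPC".

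**Use of baseline.** Section 8.1.5 picks protein spots for excision and identification by their change from baseline.

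**The concern.** A factor released by thigh ischaemia is best looked for in plasma after the cuff cycles and before anything else large has happened to the child. No specified sample falls there. The first one certain to follow the cuff is taken when bypass ends, after cardioplegic arrest, reperfusion and bypass. A protein that differs between arms at that point may be the factor itself or a consequence of a different response to bypass.

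The baseline wording adds a second problem. The cycles begin at once after induction and overlap line placement, and the blood comes from a line. Baseline may therefore fall before, during or after the cycles, and may differ from child to child. For an RIPC child with a late baseline, part of what the trial is looking for is already in the reference sample. The same draws supply the lymphocyte mitochondrial assays, so those are exposed too.

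**Working it through.** The protocol gives no figure for this point, so there is none to reproduce. The check covers the schedule and what it can identify.

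**Schedule (5.1.2, 5.1.5, 5.1.1)**
- Volume per sample: 1.5 + 5 = 6.5 ml. Total per child: 5 x 6.5 = 32.5 ml.
- Samples in the trial: 5 x 40 = 200.
- Length of the cuff cycles: 4 x 5 + 3 x 5 = 35 min, or 4 x (5 + 5) = 40 min if the last reperfusion is counted.

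**Model.** Write the mean level of a protein as a sum of four parts:
- b, the level before any intervention (equal in the two arms by randomisation);
- r, direct release by the cuff cycles;
- c, the effect of surgery and bypass;
- m, the change that RIPC makes to c.

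The model is additive and assumes that r persists to the end of bypass.

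| Design | Sham, pre-bypass | RIPC, pre-bypass | Sham, end of bypass | RIPC, end of bypass | Rank (of 4) |
|---|---|---|---|---|---|
| (a) Baseline before cuff | b | b | b + c | b + r + c + m | 3 |
| (b) Baseline after cuff | b | b + r | b + c | b + r + c + m | 4 |
| (c) Baseline before cuff plus a post-cuff, pre-bypass sample | b, then b | b, then b + r | b + c | b + r + c + m | 4 |

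**Design (a).** RIPC minus sham at the end of bypass is (b + r + c + m) - (b + c) = r + m. The net RIPC effect is estimable, and so is c, but r and m cannot be separated. The 6, 12 and 24 h samples do not help, because each brings its own c and m.

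**Design (b).** r can be estimated, but only by comparing the arms at baseline, which the protocol does not describe. Change from baseline is c in sham and (b + r + c + m) - (b + r) = c + m in RIPC, so r drops out of the section 8.1.5 selection.

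**Between (a) and (b).** If the fraction f of r is present when an RIPC child's baseline is drawn, the change from baseline in RIPC is (1 - f)r + c + m. The difference from sham is (1 - f)r + m. At f = 0 this is r + m; at f = 1 it is m. The documents give no value for f, so the range is 0 to 1.

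**Design (c).** RIPC minus sham at the added sample gives r. The end-of-bypass contrast gives r + m, and subtraction gives m. All four parts are estimable.

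**The case against.** The strongest reply is that the trial has a randomised sham arm of 20 children, who also have surgery and bypass. That stands. A reader might infer from the schedule that no RIPC effect can be separated from bypass. The documents do not support this: r + m is estimable under every design above, and it answers the primary objective and aim in section 3.1. The four post-bypass samples serve that objective directly, and section 2.2 itself goes on to name modification of the response to surgery as a goal.

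A reader might also infer that none of the 200 samples falls between cuff and bypass. That is not established either. Because baseline is undefined, up to 40 samples (one per child) could fall there. What can be said is that none is specified for that interval.

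Nor would a late baseline remove the whole RIPC effect. Only the part of r already present cancels; m remains. Section 8.1.5 uses change from baseline to choose spots, and section 10.3 names two-way ANOVA or an unpaired t test without prescribing subtraction.

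Baseline ordinarily means before the intervention. Section 5.1.2 speaks of central lines rather than the arterial line, and puts the cuff on a leg free of lines, which hints that access is settled beforehand. This makes an early draw plausible but does not fix it. If baseline is always early, design (a) applies, and r and m remain inseparable.

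Loss of a short-lived or diluted factor is speculation, since the protocol gives no kinetics and its background describes a lasting protected state. The resected myocardium (5.1.4) is taken after cardioplegia and is not plasma, so it does not fill the gap.

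**Conclusion.** The point holds in a limited form. The schedule supports the primary objective of net modification of the response to surgery. It does not support the narrower aim in section 2.2 of identifying a factor produced by the cuff cycles. With baseline before the cuff, direct release and a RIPC-altered bypass response are confounded (rank 3 of 4). With baseline after the cuff, direct release cancels from the stated spot selection. Leaving the order open means that either may apply, possibly to different children.

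The size of any cancellation, f times the direct release, cannot be given from the documents. The conclusion rests on the additive model and on r persisting to the end of bypass; if r does not persist, the post-bypass samples do not contain it. Later analysis cannot recover a sample that was not drawn, so this belongs in the protocol. It is an inexpensive improvement and not a flaw that invalidates the trial.

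**What to change.** 1. In 5.1.5, state that baseline is drawn in both arms after arterial access and before the first inflation, or the equivalent moment in sham. This needs no extra blood or assay.
2. Move one late draw, for example the 12 h sample, to after the last deflation and before bypass. The total stays at 5 x 6.5 = 32.5 ml per child and 200 samples, or 200 / 2 = 100 gels at the two samples per gel in 8.1.2.
3. Use RIPC versus sham at that sample for the circulating-factor question in 2.2, including the choice of spots for it. Keep the post-bypass comparisons for the primary objective. The new sample should not become the main test of the trial.

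**Cost.** One late time point is lost, near the 12 h clinical measurements in 4.4. Blood drawn before bypass rises from 6.5 to 2 x 6.5 = 13 ml, in children from one month of age. Adding a sixth sample instead would keep the 12 h point but raise the total to 6 x 6.5 = 39.0 ml. Whether either is acceptable is for the investigators and the ethics committee.

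If no sample is moved or added, still fix the baseline timing, and limit the aim in 2.2 to net modification of the response to surgery.

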# SUBJECT ENROLLMENT AND RANDOMISATION

- 1. **Recruitment**

Patients will be recruited by either the surgeon ([name]) or cardiologist ([name]) at the preadmission clinic or on the ward prior to surgery. The clinician ([name]/[name]) will explain to the patient’s parents/guardians, the research project, their child’s role, and outcomes and will obtain signed consent if granted.

- 1. **Eligibility Criteria**
     1. **Inclusion Criteria**

Patients with tetralogy of Fallot aged one month and older (to 18 years) having surgery for the first time.

- - 1. **Exclusion Criteria**

Patients with chromosomal defects, associated congenital lung malformations and haematological disorders will be excluded.

- 1. **Randomisation Procedures**

Random allocation is made in blocks in order to keep the sizes of the 2 treatment groups similar. In order to avoid predictability, the block size that is randomly selected is 2, 4 or 5, as the sample size must be divisible by the block size. Due to the expected relative uniformity of condition in the patient group and the small number of subjects the design will not be stratified. The randomisation will be performed in secret by a member from Heart Research (not involved in working for the trial) using SPSS statistical software generated randomisation and will place each designation sequentially in numbered envelopes 1 to 40, for patient 1 to 40 and the envelopes will be signed and sealed. The implementer of the RIPC or Sham co ntrol treatment protocols will open one envelope in numerical order immediately prior to placement of the blood pressure cuff and they will apply the RIPC treatment or sham control protocol accordingly.

- 1. **Blinding Arrangements**

[name] will not be blinded as she will be applying the RIPC treatment. She will also be involved in randomisation, sample collection, data collection, data entry and laboratory analysis. Surgeons, perfusionists, anaesthetists will be blinded. Samples will be de-identified and therefore, research laboratory staff will be blinded to the patient’s identity. The blood pressure cuff will be positioned on the thigh for both sham control and RIPC groups, however if other theatre staff witness whether the RIPC treatment protocol is invoked they will not be blinded. As these theatre staff are strictly performing standard clinical tasks and procedures and are not involved in the trial and analysis *per se*, this should not impact the blinding.

- 1. **Breaking of the Study Blind**

This will occur on completion of the final statistical analyses, and will be performed in the presence of the independent professional statistician (see 10.3).

- 1. **Subject Withdrawal**
     1. **Reasons for withdrawal**

No reason needs to be made. Only a request for withdrawal needs to be made by the subjects’ parents or guardian, (ideally prior to surgery) to [name] or [name]. It is unlikely that a parent will withdraw the subject following surgery.

- - 1. **Replacements**

In the event of a withdrawal in which the subject has not had surgery (and thus not been treated) additional recruitment will continue until n=40 subjects are completed.

- 1. **Trial Closure**

This will occur upon completion of the 40th subject.

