# STUDY VISITS AND PROCEDURES SCHEDULE

The subjects are directly studied only during the perioperative period. Blood and myocardial samples are studied upon arrival to the laboratory (mitochondrial studies) or in batches after freezing (proteomic/microscopy studies).

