**10.3 Statistical Analysis Plan**

Lab Assay analyses will be performed on coded samples by Drs [name] and [name] and the values then made available for statistical testing when all tests are complete. Statistical analyses will be performed by Drs [name], [name] & [name]. An independent professional statistician experienced in trials will be employed to check and verify the analyses prior to and after breaking the blinding. In addition to two-way ANOVA or unpaired t test, statistical analysis will employ stepwise multivariate regression and analysis of covariance tests in order to determine potential influence of age, gender, bypass time, drugs, body weight and other morphometric and clinical factors.

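### The tests named in 10.3 carry no enrolment-order term although allocation is blocked, so drift in the fresh mitochondrial assays would make them somewhat conservative and cost some power (minor)

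*Protocol*

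**What the plan says.** Allocation (Protocol 6.3, Randomisation Procedures): "Random allocation is made in blocks in order to keep the sizes of the 2 treatment groups similar". On block length, "the block size that is randomly selected is 2, 4 or 5, as the sample size must be divisible by the block size". Envelopes are numbered 1 to 40 and opened in numerical order just before the cuff is placed, so the envelope number records enrolment order.

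Accrual (5.1.1): "40 patients will be recruited in to the study within two years", with 20 children intended per arm.

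Assay timing (Study Visits and Procedures Schedule): "Blood and myocardial samples are studied upon arrival to the laboratory (mitochondrial studies) or in batches after freezing". The frozen, batched group is the proteomic and microscopy work. Mitochondrial function is part of the primary objective.

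Analysis (10.3): "In addition to two-way ANOVA or unpaired t test, statistical analysis will employ stepwise multivariate regression and analysis of covariance tests", to examine the "potential influence of age, gender, bypass time, drugs, body weight and other morphometric and clinical factors". Block, date, enrolment order and assay run are not named. The second factor of the two-way ANOVA is not identified. Only the protocol is available; a separate SAP may exist.

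**The concern.** An unpaired t test estimates its error as if the 20 and 20 children had been allocated without restriction. Here they are allocated in short consecutive runs, so each arm samples early and late periods about equally. Any slow change over two years, such as electrode behaviour, reagent lots, operator or surgical practice, then largely cancels from the RIPC-sham difference. It does not cancel from the within-arm variance that the t test uses. The reported standard error is therefore too large, the confidence interval too wide, and the real type I error below the nominal 5%.

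At stake is efficiency in a 40-child trial: a fresh mitochondrial outcome with a moderate true effect could be reported less precisely than the design allows.

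**Working it through.** **Inputs from the protocol.** 40 children, blocks of 2, 4 or 5 (6.3); fresh mitochondrial assays over two years; tests as named in 10.3; planning figures in 10.1. **Assumed:** the size and shape of the drift, two-sided alpha 0.05, and sigma 14.5 read in the same percentage units as the 20% difference.

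**1. The protocol's own figure.** For oxygen consumption, n per group = 2(1.960 + 0.842)² × (14.5/20)² = 2 × 7.85 × 0.526 ≈ 8.3, so 9. The t-based solution is 9.3, so 10, which matches the stated minimum of 10 read as per group. The planning effect is 20/14.5 = 1.38 SD; at 20 per group its power is 0.989. The inotrope calculation (n=20, sigma 3.9) states no difference; it implies 3.55, that is 3.55/3.9 = 0.91 SD, the effect with 80% power at 20 per group.

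**2. Mechanism.** With within-group SD 1 and linear drift of D SD from first to last child, drift adds about D²/12 to the variance, so the reported SE ≈ √[(2/20)(1 + D²/12)].
- D = 0: √0.100 = 0.316
- D = 1: √0.1083 = 0.329
- D = 2: √0.1333 = 0.365

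In simulation at D = 2 the reported SE was about 0.37, while the true SE of the blocked comparison was about 0.33.

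**3. Simulation at 0.91 SD.** 4,000 trials per cell, random blocks of 2, 4 or 5 cut at 40 (the odd child in a block of 5 goes to either arm at random), drift added to a within-group SD of 1. The step occurs at mid-trial.

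| Drift | Size, unadjusted | Size, order added | Power, unadjusted | Power, order added | Power, fixed blocks |
|---|---|---|---|---|---|
| none | 0.043 | 0.043 | 0.798 | 0.796 | 0.784 |
| linear 0.5 SD | 0.047 | 0.049 | 0.786 | 0.794 | 0.776 |
| linear 1 SD | 0.046 | 0.052 | 0.772 | 0.796 | 0.778 |
| linear 2 SD | 0.028 | 0.053 | 0.688 | 0.796 | 0.773 |
| linear 3 SD | 0.012 | 0.051 | 0.541 | 0.794 | 0.776 |
| step 1 SD | 0.032 | 0.046 | 0.719 | 0.768 | 0.762 |
| step 2 SD | 0.010 | 0.034 | 0.505 | 0.728 | 0.754 |

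Monte Carlo standard errors are √(0.05 × 0.95/4000) ≈ 0.003 for size and √(0.8 × 0.2/4000) ≈ 0.006 for power. A separate run gave unadjusted size 0.037 at 1 SD and 0.022 at 2 SD of linear drift, hence the rounded values of about 0.04 and 0.02 to 0.03. At 0.5 SD the differences are within or near simulation error.

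**4. Is blocking the cause?** Under complete 20:20 randomisation the unadjusted size stays at 0.046 to 0.051 for every drift from 0.5 to 3 SD, so the size below 5% comes from ignoring the blocks. The power loss is only partly specific to blocking: under complete randomisation, unadjusted power also falls, to 0.753 at 1 SD and 0.661 at 2 SD of linear drift.

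**5. The protocol's own mitochondrial effect (1.38 SD).**

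| Drift | Power, unadjusted | Power, order added |
|---|---|---|
| none | 0.988 | 0.988 |
| linear 1 SD | 0.987 | 0.992 |
| linear 2 SD | 0.974 | 0.990 |
| linear 3 SD | 0.932 | 0.988 |
| step 1 SD | 0.977 | 0.985 |
| step 2 SD | 0.909 | 0.972 |
| step 3 SD | 0.699 | 0.940 |

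**The case against.** **Drift is not documented, and parts of the design limit it.** Enzyme activities are normalised to total protein and citrate synthase, with citrate synthase read against standards; membrane-potential fluorescence is calibrated; ADP:O is a ratio. Lymphocytes are sampled five times from baseline to 24 hours after bypass, so a within-child comparison would cancel most drift over months. This stands as a reason to doubt large drift. It does not exclude drift, least of all for the single myocardial sample.

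**The planning SD may already contain the drift.** If total variance is held fixed, with drift as 20% or 40% of it and blocks of 4, unadjusted power at 0.91 SD is 0.82 or 0.86, never below the 80% target; with enrolment order it is 0.88 or 0.95. On that view power is forgone rather than lost. This is fair, though the gain from adjusting remains.

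**The term may be added elsewhere.** The second ANOVA factor is unnamed, the covariate list is open-ended, and an SAP could carry the term. One might infer that every planned test ignores the blocks; the text does not establish that. It shows only that none of the tests and covariates named in 10.3 uses the allocation structure set in 6.3. That lowers the severity.

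**Balance is not strict.** Blocks of 5 cannot split equally, and the stated purpose of blocking is similar group sizes, not drift control. This is correct, and the simulation allows for it.

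**Conclusion.** The point holds as a minor one. The named analysis does not reflect the stated randomisation, and if the fresh mitochondrial assays drift, the unadjusted comparison is conservative. At a 0.91 SD effect, adding enrolment order is worth about 2 points of power at 1 SD of linear drift (0.772 to 0.796), about 11 at 2 SD (0.688 to 0.796), about 5 for a 1 SD step (0.719 to 0.768), and nothing detectable without drift.

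A reader might infer that the primary mitochondrial comparison is at risk of a false null result. The protocol's figures do not support that for oxygen consumption: at 1.38 SD, unadjusted power stays at about 0.97 to 0.99 under linear drift up to 2 SD, and 0.91 with a 2 SD step. The loss matters mainly for smaller effects, for the other fresh assays (enzyme activities, pore opening), for which 10.1 gives no planning inputs, or for large or step-like drift. Nor does the mismatch bias the estimate or raise the false-positive rate; the error is in the cautious direction.

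The argument does not extend in the same way to the plasma proteomics, which are frozen, run in batches and carry an internal standard on each gel. All the sizes rest on assumed drift.

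**What to change.** In 10.3, state that each between-group model of the freshly run mitochondrial assays, myocardial and lymphocyte, includes envelope number as one prespecified linear covariate, kept in the model outside any stepwise selection. The unpaired t test for these outcomes then becomes an analysis of covariance with treatment and enrolment order.

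The cost is one sentence and one degree of freedom; the number is already on the envelope. Without drift the power cost is not detectable (0.798 against 0.796). Fixed block effects are not needed: they cost about 1 to 2 points without drift (0.784 against 0.798 in one set of runs, 0.784 against 0.803 in another). A linear term does not fully absorb a step: with a 2 SD step, size is 0.034 and power 0.728, against 0.754 with fixed blocks. It still recovers most of the loss from 0.505.

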# STATISTICAL METHODS

**10.1 Sample Size Estimation**

Sample size is based primarily on the successful study of RIPC in children (see ref 17) where n=approximately 20 per treatment group. This prior study was amply powered to detect differences in clinical and molecular measures. Notably, post-operative inotrope usage was greatly diminished by RIPC. Based on these inotrope usage results, a power of 0.8, alpha=0.05 and sigma of 3.9 indicates that a sample size of n=20 was required. Injury was deemed to be diminished by RIPC on the basis of reduced troponin I release, thus for a power of 0.8, alpha of 0.05 and a sigma of 3 the sample size required is calculated as n=16. Based on our laboratory’s ability to detect a 20% difference in mitochondrial oxygen consumption in human tissue preparations at least 10 subjects are required to detect this difference (power=0.8, sigma=14.5, alpha=0.05, 2 groups. Similarly, the detection of changes in many mitochondrial proteins measured by proteomic assays, are also quite sensitive ranging between 10-20%. Thus a sample size of n=20 per group will yield ample statistical power.

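### A permitted block size of 5 cannot split equally between two arms, so the stated 20/20 allocation is not guaranteed; the effect is minor

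*Protocol*

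**What the plan says.** Section 5.1.1 of the protocol fixes the allocation: "They will be randomized into 2 equal sized groups", with 20 patients named for sham and 20 for RIPC. Section 10.1 plans on the same number: "Thus a sample size of n=20 per group will yield ample statistical power".

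The Randomisation Procedures give the purpose of blocking: "Random allocation is made in blocks in order to keep the sizes of the 2 treatment groups similar". The size is varied so that allocations are harder to guess, and the rule for choosing it reads: "the block size that is randomly selected is 2, 4 or 5, as the sample size must be divisible by the block size". There is one list, because with "the small number of subjects the design will not be stratified", and it fills "numbered envelopes 1 to 40, for patient 1 to 40".

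The protocol does not say:
- whether one size is drawn for the whole list or a new size for each block;
- with what probability each size is drawn;
- how a block of 5 is divided between the arms;
- what happens if a block runs past patient 40.

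**The concern.** The reason given for the block sizes is that each divides 40. That ensures only that a list built from a single size ends on a complete block. It does not make any block balanced. Balance requires the block size to be a multiple of the number of arms. Sizes 2 and 4 meet that condition and size 5 does not.

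The section on randomisation therefore allows lists that section 5.1.1 rules out. What is at stake is agreement between two parts of the protocol, and a blocking scheme that does what blocking is for. The validity of the comparison is not at stake.

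A secondary question is predictability. In a block of 2 the second allocation is the opposite of the first, and the person who opens the envelopes in numerical order sees every past allocation.

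**Working it through.** **Inputs from the protocol.** Total 40; two arms; 20 per arm; block sizes 2, 4, 5; no stratification. For the effect on power, section 10.1 gives alpha 0.05, power 0.8, sigma 3.9 and n = 20 for inotrope use. I read n = 20 as per group and assume a two-sided test.

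**Assumptions that the protocol does not state.** A 5-block is 3:2 or 2:3 with probability 1/2 each. Sizes 2, 4 and 5 are drawn with probability 1/3 each.

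**Step 1: the two divisibility tests.**

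| Block size | 40 mod size (the protocol's test) | size mod 2 arms (the test needed) |
|---|---|---|
| 2 | 0 | 0 |
| 4 | 0 | 0 |
| 5 | 0 | 1 |

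All three sizes pass the protocol's test. Size 5 fails the one that matters.

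**Step 2: one size for the whole list.** With size 5 there are 40/5 = 8 blocks. If k of them are 3:2 in favour of RIPC, the RIPC arm has 16 + k patients.
- P(20/20) = C(8,4)/2^8 = 70/256 = 27.3%, so P(unequal) = 72.7%.
- The range is 16/24 to 24/16. The two extremes together have probability 2/256 = 0.8%.
- If every 5-block were split the same way, the result would be 24/16.

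Sizes 2 and 4 always give 20/20. Over the three possible draws, P(unequal) = 72.7%/3 = 24.2%, so 75.8% of lists are 20/20.

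**Step 3: a new size for each block.** I summed over all block sequences, exactly rather than by simulation.

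| End of list | P(20/20) | P(difference of 4 or more patients) |
|---|---|---|
| Cut at patient 40 | 37.7% | 13.6% |
| Only sequences totalling exactly 40 | 41.4% | 9.5% |

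**Step 4: even sizes only.** With sizes 2 and 4 and blocks totalling exactly 40, every list is 20/20. If the last block may be cut at patient 40, 88.9% are 20/20 and the rest are 21/19.

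**Step 5: effect on power.** By the normal approximation, the difference that has 80% power at 20/20 is 3.9 × (1.960 + 0.842) × √(2/20) = 3.455. Power at a/b is Φ(3.455 / (3.9 × √(1/a + 1/b)) − 1.960). At 24/16 this is Φ(2.745 − 1.960) = 78.4%.

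| Split | 20/20 | 21/19 | 22/18 | 23/17 | 24/16 |
|---|---|---|---|---|---|
| Power | 80.0% | 79.9% | 79.6% | 79.1% | 78.4% |

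**Step 6: predictability.** If the current block is known to be a 2, its second allocation is certain. If the size is unknown and drawn equally from 2, 4 and 5, the chance that the second allocation on the list is the opposite of the first is (1 + 2/3 + 3/5)/3 = 75.6%.

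**The case against.** The strongest reply is that nothing of consequence follows.

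- **The stated aim is similar groups, not identical ones.** This is true of the Randomisation Procedures. Section 5.1.1, however, says equal and gives 20 and 20, so the two sections still need to be reconciled.
- **The analyses tolerate unequal groups.** The t test, ANOVA and analysis of covariance in section 10.3 do not need 20/20, and the loss of power is under 2 points even at 24/16. This stands, and it is why the point is minor.
- **The natural reading is a single size for the whole list.** The wording is in the singular, and divisibility of 40 makes sense only on that reading. About 76% of lists are then 20/20, and an incomplete last block cannot arise. This is fair, but the text does not settle the matter, and the reading still leaves a one-in-three draw of a size that is unequal in 73% of lists.

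Three stronger readings are tempting, and the protocol does not support them.

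- **That 20/20 cannot be reached.** It can: four 3:2 blocks and four 2:3 blocks give it. It is only not guaranteed.
- **That every second allocation in a pair is certain.** That holds only for someone who knows or infers that the block is a 2, most clearly if 2 is the single size throughout.
- **That selection bias follows.** The surgeon or cardiologist recruits, surgeons are stated to be blinded, and the envelope is opened just before the cuff is placed, after consent. The protocol does not show that the person opening it decides who enters or when. That person's part in randomisation and data handling is a separate question of blinding.

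**Conclusion.** The stated rule is wrong, and it conflicts with section 5.1.1. A block of 5 cannot give 1:1, and nothing in the protocol pairs 3:2 blocks with 2:3 blocks.

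How often the list would be unequal depends on the reading: about 24% of lists if one size is drawn for the whole trial, and about 59% to 62% if the size is redrawn for each block (100% − 41.4% and 100% − 37.7%). These figures rest on the two assumptions above and on each of the 40 envelopes being used once.

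The defect is minor. Allocation remains random and unbiased, and the cost in power is at most about 1.6 points over splits up to 24/16 (80.0% − 78.4%). It should be corrected because the correction is easy and the two sections disagree, not because the trial's conclusions would be at risk. The predictability of blocks of 2 is a secondary, conditional point.

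**What to change.** **Required.** In the Randomisation Procedures:
1. Remove block size 5.
2. State that only even block sizes are used, in random order, constrained to total exactly 40.
3. Replace the reason given with the requirement that the block size be a multiple of the number of arms.
4. Keep the block sizes out of documents that trial staff see.

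**Optional.** Avoid 2 as the only block size, or use larger even blocks. Four blocks of 4 and four of 6 in random order would do, since 16 + 24 = 40. This lowers predictability but is not needed to restore 20/20.

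**Cost.** One sentence and a regenerated list before the first envelope is opened. There is no change to sample size, procedures or timeline.

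**If envelopes have already been opened.** Regenerate only the unopened ones, counting the allocations made. With r patients already in RIPC and s in sham, the remaining envelopes must hold 20 − r and 20 − s. Balanced even blocks for the remainder alone would carry any existing imbalance to the end. The change and its date should be recorded.
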